#### Recruitment

Participants for the SUD group will be recruited from a male-only, age-restricted inpatient drug rehabilitation facility in Cajititlán, Mexico. Eligibility criteria include being male, aged 18-59 years, and actively participating in a therapeutic community treatment program for SUD, with a cognitive behavioral therapy approach. Furthermore, candidates must undergo their first rehabilitation attempt within this specific program and be under medication management for any possible mental health comorbidity diagnosed with the Mini International Neuropsychiatric Interview (MINI) or physical disease. Finally, participants are required to review the privacy and safety terms and provide informed consent before joining the study. Smartwatches will be synchronized with a community smartphone by the personnel of the rehabilitation center, in accordance with the restricted access to smartphones.

#### Control Participants

Control group participants will be recruited through an open call for volunteers in the ZMG area, restricting the sampling to similar sex and age characteristics of the patients from the rehabilitation facility. To be eligible, individuals must be male, aged 18-59 years, have no history of SUD, either diagnosed or self-reported, with no current use of substances, excluding caffeine. They must review and agree to the privacy and safety terms, as well as the requirements for active participation. In addition, participants are required to commit to a six-month study period, synchronize and upload their data weekly, and attend scheduled meetings with the research team. In case an individual is interested in participating in the study, but does not have access to a personal smartphone, a device will be provided.

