### Demographic and Psychological Assessment

Demographic information, such as age, place of birth, education, occupation, civil status, household income, housing characteristics, as well as medical and family history, will be collected at baseline. A form will be filled in by the participant, assistance from the trained research staff will be provided if it is required.

The psychological tests will be administered at baseline within the first 15 days of participation. A battery of self-report questionnaires has been chosen to assess for a history of childhood trauma (Adverse Childhood Experiences Assessment [ACEs]) [68], the presence of depression or depressive symptoms (Beck Depression Inventory [BDI-II]) [69], anxiety and stress (Beck Anxiety Inventory [BAI-II]) [70], sleep disorders (Pittsburgh Sleep Quality Index [PSQI]) [71], and short-term memory (Wechsler Adult Intelligence Scale IV [WAIS-IV] subtests: Digit Span and Letter-Number Sequencing) [72]. Substance use–specific tests will aim to determine the type of substance, frequency and quantity of used drugs (Alcohol, Smoking and Substance Involvement Screening Test [ASSIST]) [73], level of substance craving (Mannheimer Craving Scale [MaCS]) [74], as well as the stage or frame of mind of the individual starting the therapeutic process (University of Rhode Island Change Assessment Scale [URICA]) [75].

To obtain a comparative measurement after treatment, depression, anxiety and stress, sleep disorders, short-term memory, stage of change and craving, will be reevaluated within fifteen days before the sixth month period of digital tracking ends (Figure 3).

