### Outcomes

#### Profiles

A total of 4 distinct subprofiles will be generated based on the results of the statistical analysis: (1) demographic, (2) psychological, (3) craving, and (4) digital biomarkers. These profiles will subsequently be integrated to create digital phenotypes for individuals with SUD.

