#### Predictive Model

A predictive model will be developed to distinguish between healthy individuals and patients with SUD. In addition, the model will predict the duration of a rehabilitation therapeutic program and the length of sobriety adherence for individuals rehabilitated using the center’s methodology. A minimum performance threshold of AUC≥0.8 and F2≥0.8 has been established to evaluate the model as fully functional.

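### Controls resemble patients demographically only in sex and age, so demographic differences cannot be credited to the SUD phenotype or allowed to carry the healthy-versus-SUD model past its 0.8 thresholds

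*Protocol article*

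**What the plan says.** **Where the groups come from.** Recruitment says that patients are "recruited from a male-only, age-restricted inpatient drug rehabilitation facility in Cajititlán, Mexico". Control Participants says: "Control group participants will be recruited through an open call for volunteers in the ZMG area". The only demographic alignment that this section describes is "restricting the sampling to similar sex and age characteristics of the patients from the rehabilitation facility". Controls must also "have no history of SUD, either diagnosed or self-reported, with no current use of substances, excluding caffeine", stay for six months, upload data weekly and attend meetings. The Exclusion Criteria are the same for both groups. None of these conditions aligns the groups on social or economic characteristics.

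**What is collected.** Demographic and Psychological Assessment lists "age, place of birth, education, occupation, civil status, household income, housing characteristics, as well as medical and family history".

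**How it is used.** Goal and Objectives names the demographic profile among the model's inputs. Sample Size counts it as one of four independent variables. Profiles lists it first of four subprofiles and adds: "These profiles will subsequently be integrated to create digital phenotypes for individuals with SUD". The abstract's Methods paragraph says that the phenotype arises from comparing the profiles with controls.

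**What is judged.** Predictive Model states: "A predictive model will be developed to distinguish between healthy individuals and patients with SUD". It then adds the duration and sobriety predictions, and sets a minimum AUC and F2 of 0.8 for calling the model fully functional. It names no inputs for the healthy-versus-SUD task. Data Preprocessing selects features by a filter on their correlation with the target.

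**The concern.** In a comparison of patients from one centre with self-selected volunteers, the control distribution of any unaligned variable depends partly on who volunteers, can attend a university site and will keep up a six-month commitment. Education, occupation, income and housing are the kind of variable on which such groups tend to differ. A classifier trained on them can learn recruitment source and report it as SUD status. A filter that keeps features correlated with the target would favour exactly those items.

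Two claims are at stake. The first is that the healthy-versus-SUD model has met its thresholds on the strength of wearable, psychological and craving data. The second is that the integrated phenotype describes people with SUD rather than, in part, how the comparison group was found. Limitations and Considerations mentions convenience sampling of patients and the sex and age limits, but only as limits on generalizability. It does not mention differences between the groups that arise from their source.

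**Working it through.** The protocol gives no figure for demographic imbalance, so there is nothing of its own to reproduce. The question is how large an imbalance would have to be to reach 0.8 with no contribution from any other data. **Every imbalance below is an assumption.** Only the 0.8 thresholds (Predictive Model) and the 25 per group (Sample Size) come from the document.

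**1. One binary item.** AUC = 0.5 + (p1 − p0)/2.
- 80% of controls against 20% of patients: 0.5 + 0.60/2 = 0.80.
- 60% against 20%: 0.5 + 0.40/2 = 0.70.
- 50% against 30%: 0.5 + 0.20/2 = 0.60.

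**2. F2 for the 80/20 item.** Classify as SUD when the item is absent. Recall is 0.80. With equal groups, precision is 0.80/(0.80 + 0.20) = 0.80. F2 = 5 × 0.80 × 0.80 / (4 × 0.80 + 0.80) = 3.2/4.0 = 0.80. That single item meets both thresholds.

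**3. Several independent, normally distributed items, each shifted by D SD.** AUC = Φ(√k × D/√2).
- k = 4, D = 0.6: √(4 × 0.36) = 1.2; 1.2/√2 = 0.849; Φ(0.849) = 0.80.
- The shift needed for AUC 0.80 is 0.842 × √2 = 1.19 SD on one item, or 1.19/√5 = 0.53 SD on each of five.

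**4. Five items at the planned size.** These figures come from 1,000 simulated data sets per row, with 25 per group, five-fold cross-validated linear discriminant analysis, independent items and no other signal. Only AUC was simulated, not F2.

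| Shift per item (SD) | Theoretical AUC | Mean cross-validated AUC | Runs with AUC ≥ 0.80 |
|---|---|---|---|
| 0 | 0.50 | 0.49 | 0% |
| 0.2 | 0.62 | 0.54 | 0.4% |
| 0.5 | 0.79 | 0.72 | 19% |
| 0.8 | 0.90 | 0.85 | 82% |
| 1.0 | 0.94 | 0.91 | 99% |

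Small imbalances do no harm. At 0.5 SD on each of five items the threshold is passed about one time in five, and at 0.8 SD it is usually passed.

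**5. Which outputs are exposed.** The five labels under Output (timely or late rehabilitation; early relapse, late relapse or maintenance) apply to patients with SUD only. Controls play no part in them, so the problem is confined to the healthy-versus-SUD model and the phenotype.

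**The case against.** **The target is secondary.** The stated purpose is to predict duration and relapse, and the hypothesis in Principal Findings attaches the thresholds to that model. Healthy versus SUD is one sentence under Predictive Model. This stands. A reader might infer that the main relapse prediction is compromised, but the labels are all within SUD, so the document does not support that.

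**The protocol does not say that demographics enter this classifier.** Predictive Model lists no inputs, and Data Preprocessing names only wearable, psychological and craving data for scaling and integration. This also stands, so it would be wrong to say that the plan feeds demographics into the healthy-versus-SUD model. But Goal and Objectives and Sample Size both count the demographic profile as an input, and nothing excludes it here. Its place in the phenotype is explicit.

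**Some difference is genuine.** A reader might infer that the demographic differences are purely a sampling artefact. The abstract's Background and the Introduction tie SUD to unemployment and socioeconomic disadvantage, so real differences are to be expected. What stands is that the two sources cannot be told apart.

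**The magnitudes are invented.** No demographic data are given, and the 80/20 split was chosen to give 0.80. Education, occupation, income and housing are plausibly correlated, which lowers the combined AUC when all differences run in the same direction. The figures show what is possible, not what will happen.

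**Detail belongs in an analysis plan.** Feature lists and adjustment commonly do. The composition of the phenotype, its comparison with controls, the control source and the thresholds do not wait for such a plan: the article fixes them.

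**Part of the route is eased.** Controls without a smartphone are lent one. That removes one economic barrier and leaves the others.

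**Conclusion.** The point holds in a limited form. The groups are demographically aligned only on sex and age, while demographics are a named input and part of a phenotype defined against controls. Demographic differences therefore mix possible correlates of SUD with recruitment source, and the design offers no means of separating them. If demographics are used in the healthy-versus-SUD model, AUC and F2 of 0.8 would not show that the band, psychological or craving data carry information.

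The size depends on an unknown imbalance. Reaching AUC 0.80 from demographics alone takes roughly a 60-percentage-point difference on one binary item, or about 0.53 SD on each of five independent items before any loss from model fitting. The document supports neither a claim that this will occur nor any doubt, on this ground, about the duration and relapse models.

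**What to change.** In Profiles and Predictive Model:

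1. State that the healthy-versus-SUD model is judged against the 0.8 thresholds without the demographic profile.
2. Report the AUC of a demographics-only model beside it as a benchmark.
3. Present SUD-control demographic differences as a description of the two samples, not as part of the phenotype.
4. Keep demographics in the within-SUD duration and relapse models.

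Adjustment of SUD-control comparisons for education can be added as a sensitivity analysis. Adjustment for household income should not be the main analysis: income may be a consequence of SUD, and adjusting for it could remove part of a real difference.

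**Cost.** A few sentences and one extra model, using data already collected. The healthy-versus-SUD AUC will probably be lower. Results reports the data at the labelling and preprocessing stage in June 2025 with recruitment open to January 2027, so the change can still be made before the models are judged.

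**What this leaves.** Other differences tied to source remain, notably pen-and-paper against computer-based testing (Participant Identification and Randomization) and the centre's fixed daily schedule (Limitations and Considerations). Dropping demographics removes only the most direct route, and the limitations should say so.

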**Methods:**

The study will be conducted with adult male patients with SUD at a rehabilitation center and control volunteers. Participants will undergo a self-reported demographic and psychological assessment, a clinician-administered craving and emotional reaction test, and will also be monitored using a smartwatch. SUD participants will be monitored for a total of 18 months (6 months during rehabilitation, an additional 12 months post discharge), and control participants for a total of 6 months. All participants will be reassessed at the sixth month of monitoring. The collected data will then be used to train models with a neural network, which will then be validated against other models and compared with other algorithms. Demographic, psychological, digital biomarkers, and craving profiles will be created, correlations will be analyzed, and they will be compared with controls to generate a digital phenotype of SUD. When the model achieves adequate validity (area under the curve of ≥0.80), a graphic user interface will then be designed for clinical use.

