### Statistical Analysis

Statistical analysis will be conducted using R-Studio IDE (version 4.3.1; Posit PBC), Prism GraphPad (version 9, GraphPad Software Inc), and MATLAB (version R2025a, MathWorks Inc). A descriptive analysis of normality (Shapiro-Wilkin normality test) means and medians, SD and error, variance (ANOVA or Kruskal-Wallis tests) will be performed. Correlation analyses (Spearman or Pearson) will be conducted to gain a preliminary understanding of the interactions between variables, as well as using time series analysis descriptive models to identify patterns, trends and cycles of activities by participants, and by groups. MATLAB will be used for advanced data processing and visualization, ensuring robust and comprehensive analysis.

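### The SUD-control comparisons behind the digital phenotype name no age adjustment, while controls are aligned on age only loosely; a systematic age gap could be read as an SUD effect

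*Protocol article*

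**What the plan says.** **Age limits.** The Recruitment section sets "Eligibility criteria include being male, aged 18-59 years" for patients. The Control Participants section sets the same limits for volunteers: "individuals must be male, aged 18-59 years, have no history of SUD".

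**Alignment on age.** Controls come from an open call, "restricting the sampling to similar sex and age characteristics of the patients from the rehabilitation facility". The article gives no matching ratio, age strata, caliper or balance check.

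**Named tests.** Within a descriptive analysis, the Statistical Analysis section says that "variance (ANOVA or Kruskal-Wallis tests) will be performed". It adds: "Correlation analyses (Spearman or Pearson) will be conducted to gain a preliminary understanding of the interactions between variables". Neither statement names a covariate.

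**Use of the results.** The Abstract (Methods) says of the profiles that "they will be compared with controls to generate a digital phenotype of SUD". The Profiles section says: "A total of 4 distinct subprofiles will be generated based on the results of the statistical analysis". The four are then integrated into the phenotype.

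**Availability of age.** The Demographic and Psychological Assessment section lists it among the baseline items: "Demographic information, such as age, place of birth, education".

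**The concern.** The groups are not randomised. One consists of residents of a single inpatient facility and the other of community volunteers, so nothing in the design makes their ages equal beyond the instruction to sample similarly. Smart-band features such as resting heart rate, sleep timing and activity can be expected to vary with age. A comparison without an age term then mixes the age difference with the SUD difference.

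The tests are introduced as descriptive, but their output is used: it builds the profiles, and the profiles build the phenotype. An age-driven difference could therefore enter the phenotype as a characteristic of SUD. Because the bias is systematic, recruiting more participants would not remove it.

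**Working it through.** **Inputs from the article.** Age limits 18 and 59 (Recruitment; Control Participants). Minimum of 25 per group (Sample Size). Confidence level 95%, taken as two-sided 5%. The article gives no figure for age imbalance or for age-feature correlation, so there is no stated figure to reproduce.

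**Assumptions.** Ages are spread evenly over 18-59, so SD = 41/√12 = 11.84 years. The within-group correlation r between age and a feature is 0.3 to 0.5. The relation is linear, and SUD has no true effect on the feature.

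**Step 1: bias.** Bias in SD units = r × gap / 11.84.

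- 5-year gap: 5/11.84 = 0.422, so bias is 0.3 × 0.422 = 0.13 to 0.5 × 0.422 = 0.21 SD.
- 10-year gap: 10/11.84 = 0.845, so bias is 0.3 × 0.845 = 0.25 to 0.5 × 0.845 = 0.42 SD.

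The sign is that of r × gap. A feature that rises with age is biased one way and a feature that falls with age the other way.

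**Step 2: false-positive rate.** Two-sample t test, 25 per group, 48 degrees of freedom, noncentrality = bias × √(25/2).

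| Gap | r | Bias (SD) | Noncentrality | Rejection rate |
|---|---|---|---|---|
| 5 years | 0.3 | 0.13 | 0.45 | 7.2% |
| 5 years | 0.5 | 0.21 | 0.75 | 11.3% |
| 10 years | 0.3 | 0.25 | 0.90 | 14.2% |
| 10 years | 0.5 | 0.42 | 1.49 | 31.0% |

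At weaker correlations of 0.1-0.2, a 5-year gap gives only about 5.2-6.0%.

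**Step 3: chance imbalance.** If both groups came from one age distribution, the standard error of the difference in mean age would be 11.84 × √(2/25) = 3.35 years, a 95% range of ±6.6 years. The standard error of the unadjusted test already allows for imbalance of this kind, and the overall type I error stays at 5%. On that model a gap of 10 years or more has probability about 0.003. The rates in Step 2 therefore apply to a systematic gap, not to chance imbalance.

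**Step 4: precision.** Variance of the adjusted difference relative to the unadjusted one = (1 − r²)/(1 − R²), where R² = d²/(d² + 4) and d is the age gap in SD units.

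- No gap: 0.91 at r = 0.3 and 0.75 at r = 0.5, a reduction of 9-25%.
- 5-year gap (R² = 0.043): 0.95 and 0.78.
- 10-year gap (R² = 0.151): 1.07 and 0.88. At r = 0.2 it is 1.13.

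Adjustment improves precision when ages are balanced. It can cost some when they are not and the correlation is weak.

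**The case against.** The case against has several parts.

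- **Silence is not a plan to leave age out.** The article condenses a longer document, the tests sit under a descriptive heading, and an analysis plan that is not shown may add covariates. Naming ANOVA does not rule out further terms. This stands as a limit: the documents do not support saying that the trial has decided against adjustment. The point is only that the methods actually named carry no age term and that their results have a stated use.
- **The design does address age.** Controls are to be similar in age to the patients, over and above the shared limits. This also stands. A reader might infer that the groups do differ in age, but the documents give no ages by group.
- **The chance range of 6.6 years is not evidence of bias.** Correct, as Step 3 shows.
- **The largest error rates need a 10-year gap and assumed correlations.** Correct. They are an upper illustration and not an expectation.
- **Unadjusted tests do not always lose precision.** Correct, as Step 4 shows. A reader might infer a general loss, but the direction depends on the balance of ages.
- **Age is not ignored.** It is recorded, and a demographic profile is integrated with the others. But placing age beside the other features does not take it out of the comparisons that build the biomarker and psychological profiles.
- **The main objective is hardly touched.** The five output labels concern therapy duration and relapse among patients, and none involves controls. This limits the scope of the point.

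What remains is a non-randomised comparison with loosely specified age alignment, tests without an age term, and a stated use of the result.

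**Conclusion.** The point holds as a risk that is cheap to remove. If SUD patients and controls differ systematically in age, age-related features in the profiles are biased by 0.13-0.21 SD for a 5-year gap, with a false-positive rate of about 7-11% at 25 per group. For a 10-year gap the figures are 0.25-0.42 SD and about 14-31%, but that would mean the age restriction had worked poorly. All of this rests on an assumed age SD of 11.8 years, assumed correlations of 0.3-0.5 and a linear relation. With weaker correlations the effect is small.

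Bias is the reason to act. Precision is secondary: it may improve with balanced ages and may worsen somewhat without them. The conclusion applies to the SUD-control profiles and phenotype and does not extend to the within-SUD predictions of relapse and therapy duration.

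**What to change.** For each continuous feature entering the profiles, estimate the SUD-control difference from a linear model with group and baseline age, using heteroscedasticity-robust standard errors. For clearly non-normal features use a rank-based or transformed version. Build the profiles from the age-adjusted differences and report the unadjusted ones beside them.

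**Cost.** Analysis wording only. Age is already collected, and the Results section places the data at labeling and preprocessing, so the change can be made before analysis. Each model spends one degree of freedom and assumes a form for the age relation. If ages differ, some precision may be lost: about 7% more variance at a 10-year gap with r = 0.3.

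**Limit.** This change covers the profile comparisons. It does not alter the correlation filter in Data Preprocessing or the SUD-versus-healthy classifier in Predictive Model.

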#### Exclusion Criteria

The exclusion criteria have been established for both groups equally. Individuals with physical conditions that significantly affect mobility, impede the use of a smart band or the registry of facial expressions, such as facial (eg, craniofacial abnormalities, facial nerve palsies, or severe neurological conditions) or neurological disorders, are ineligible. In addition, patients with a history of heart conditions, breathing issues, as well as significant vision and hearing impairment will be excluded, as these conditions might affect the measurements.

